#### 2.5.3. Permitted and Prohibited Concomitant Treatments

All the participants will receive identical SLT. The treatment period is 4 weeks (3 treatment sessions per week, alternate days), resulting in a total of 12 sessions. Speech therapy will be performed by an experienced language therapist who received standardized training in language rehabilitation.

The language rehabilitation training method will be as follows: first, the patients will be assessed for their language function and scored, and then a training plan and training principles will be formulated according to the type of aphasia and language ability; the training is progressively followed by targeted strengthening exercises. The main content includes motor training of pronunciation organs, oral pronunciation training, naming, intonation, etc. (1) Mouth shape and voice training: at the beginning of the training, patients will be taught to control their lip and tongue movements through mouth shape and voice control to practice pronunciation. The patients will practice the rhymes and consonants first and then gradually transition to the differentiation of approximate sounds. (2) Use of language training equipment (cell phones, iPads, etc.): patients can use phrases and sentences from daily life to make audio files that are suitable for reading. The patients will practice the phrases first, and then, the sentences. (3) Training the pronunciation muscles: patients with aphasia may have different degrees of wasting atrophy of the pronunciation-related muscles, which results in slurred speech. During training, patients are instructed to practice tonal movements of the tongue and oral muscles to promote accurate pronunciation. (4) Regular check-ups and weakness reinforcement exercises: weaknesses in pronunciation for targeted exercises will be identified, and individual reinforcement training for patients will be provided if necessary.

### 2.6. Sample Size Calculation

No large RCTs have been carried out within the field examining the long-term effects of acupuncture on PSA. Previous studies have used interventions not applicable to the current protocol and have been of varying quality and used small sample sizes. We were, therefore, unable to calculate the prior accurate sample size. Thus, our RCT will support a more accurate sample size estimate and inform a definitive trial examining the long-term effectiveness of acupuncture for aphasia. The study involves the experimental study of functional magnetic resonance imaging (fMRI) and EEG for language tasks, which falls under the scope of experimental psychology. Taking into account individual psychological differences, it is expected that the PSA patients to be included will be divided into 2 groups. The number of patients to be included in the statistics in each group will be 20. Considering a drop-out rate of 20%, the target recruitment number is 48 participants (24 per group).

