### 2.2. Randomization and Blinding

Eligible patients will be randomly assigned to the acupoint group or NA control group with a 1 : 1 ratio. The randomization sequence will be generated by a third-party professional statistician using a computer-generated randomization digital table using SAS V.9.4 software (SAS Institute Inc., North Carolina, USA). An independent assessor will interview the participants and carry out the screening. Random numbers and group assignments will be confirmed immediately through short message service to the practitioners who conduct acupuncture. All participants will be blinded to the types of acupuncture. An independent, blinded assessor who does not know the group assignment will conduct the outcome evaluation after the treatment. The researcher who will oversee the statistical analysis will also be blinded, with the treatment for each group remaining unknown; however, it is impossible to blind practitioners who conduct acupuncture. The practitioner will be forbidden from discussing the type of acupuncture with the participants. We will endeavour to ensure that subjects begin the trial with similar expectations of efficacy by informing them that the provided treatments are effective. In this study, participants, assessors, and statisticians will be blinded to treatment allocation. Participants will receive treatments alone at different times to avoid communication with each other. An eye patch will be applied to patients during the acupuncture treatment. To minimize the unintentional physical cues and bias in this trial, acupuncturists will be required to emulate the same procedure for the nonacupoint control group. In addition, participants will be asked to answer the following question during week 4 to test the blinding effect: “Do you think you have received real acupuncture treatment?” The participants can choose “yes” or “no” as an answer [37, 38]. The percentage of participants who answered “yes” in both groups after the final treatment will be analyzed. If the results show no significant difference in the response to this question between the two groups, they could suggest that the blinding effect is sufficient.

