### 2.9. Statistical Analysis

#### 2.9.1. Clinical Data Analysis

All statistical analyses will be performed by a statistician from the Clinical Evaluation and Analysis Centre of Dongzhimen Hospital affiliated to BUCM using Statistical Package for the Social Sciences (SPSS) V.22.0. The statistician will be blinded to the allocation of groups. The level of significance is established at *α* < 0.05 with a two-tailed test. The main objective is to compare the change in the AQ score at week 12 from baseline between the acupoint group and the NA control group. The null hypothesis is that the acupoint group will show the same change as the NA control group, while the alternative hypothesis is that the acupoint group shows a greater improvement. Categorical data will be represented by percentages, whereas continuous data will be represented by the average, standard deviation, median, minimum value, and maximum value. For comparison with the baseline, a *t*-test or nonparametric test will be used for continuous data and nonparametric tests for categorical data. For comparison of two independent samples, if the residuals are normally distributed, the analysis of covariance (ANCOVA) will be used for the primary outcome and subgroup analysis stratified by aphasia severity, *t*-tests for other continuous data, and chi-square tests for categorical data; if the residuals are non-normally distributed, a nonparametric test will be used for both the continuous and categorical data. The results of the intention-to-treat (ITT) analysis will be used to assess the validity of the study as a whole. The ITT analysis will collect data from all the participants in this trial, and for those lost to follow-up, the last observation carried forward method will be implemented.

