Regarding the study design, we developed an assessor- and participant-blinded design to minimize bias. The specific effects are thought to be generated by needling the acupoint with the appropriate manipulation. The nonspecific effects are due to other aspects of the therapy, such as the expectations of the patient, which might influence the treatment outcome. To recognize the specific effects, a placebo is needed. Among acupuncture research, placebo controls for acupuncture studies have been difficult to select. To maximally exclude the placebo effect, rigorous methodological designs are followed. In our study, control conditions involve being punctured with real acupuncture needles at NA locations. Thus, the self-perception of placebo effects in the NA control group is difficult to distinguish from the real acupoints. Additional needle manipulations will not be used in the NA control group. De qi is a characteristic constellation of sensations felt by patients during acupuncture needling. It has been regarded as an important factor related to clinical effects; however, we do not pursue this kind of sensation in the NA control group. By following these methods, participants can be successfully blinded, and the efficacy of acupuncture could be confirmed if the results of the acupoint group prove superior to those of the NA control group.

We will assess patients with PSA on multiple levels, including multiple neuropsychological tests, functional and structural brain alterations, and TCM syndrome evaluation. This multidomain assessment will be used to identify possible biomarkers involved in the effects of acupuncture in PSA.

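### At the stated 20% drop-out, 24 recruits per group leave about 19 completers, not the 20 the sample size section says will be analysed

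*Protocol article*

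**What the plan says.** Section 2.6 of the protocol article fixes the number of patients who will enter the analysis: "The number of patients to be included in the statistics in each group will be 20". The next sentence gives the recruitment target: "Considering a drop-out rate of 20%, the target recruitment number is 48 participants (24 per group"). Section 2.2 sets equal allocation: "Eligible patients will be randomly assigned to the acupoint group or NA control group with a 1 : 1 ratio".

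The 20 per group is not derived from an effect size, a standard deviation or a power. Section 2.6 is open about this: "We were, therefore, unable to calculate the prior accurate sample size". It adds that "our RCT will support a more accurate sample size estimate and inform a definitive trial examining the long-term effectiveness of acupuncture for aphasia".

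Section 2.9.1 plans an intention-to-treat analysis in which, "for those lost to follow-up, the last observation carried forward method will be implemented". It names ANCOVA for the primary outcome (change in aphasia quotient at week 12) when residuals are normal, tested two-sided at 5%.

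**The concern.** Two adjacent sentences contain three linked figures: 20 analysable per group, 20% drop-out and 24 recruited per group. Any two of them determine the third, and the three do not agree. A drop-out rate is ordinarily a share of those recruited, so the recruitment target should be the analysable number divided by the proportion who stay. Adding 20% of the smaller number gives too few.

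What is at stake is the accuracy of the statement that fixes the trial's size. At the plan's own drop-out rate, the expected number of patients with observed outcomes falls short of the number promised. A reader who later compares completers with plan would be comparing against a figure the design was not expected to deliver.

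**Working it through.** **Inputs**

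- Analysable patients per group: 20, so 40 in total (section 2.6).
- Drop-out: 20%, so a retained proportion of 1 − 0.20 = 0.80 (section 2.6).
- Recruits: 48, or 24 per group (section 2.6), allocated 1:1 (section 2.2).

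**Step 1: reproduce the stated target.** Multiplying by one plus the drop-out rate gives 20 × 1.20 = 24 per group and 40 × 1.20 = 48 in total. Both match exactly, so this is evidently how the target was obtained.

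**Step 2: apply the stated drop-out to the stated target.** Completers = recruits × (1 − drop-out).

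- Per group: 24 × 0.80 = 19.2, against 20 stated. The shortfall is 0.8.
- In total: 48 × 0.80 = 38.4, against 40. The shortfall is 1.6.

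**Step 3: find what would make the three figures agree.** There are three ways, each holding two figures and solving for the other.

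| Held fixed | Solved for | Result |
|---|---|---|
| 20 completers per group, 20% drop-out | recruits = 20 / 0.80 | 25 per group, 50 in total |
| 24 recruits per group, 20% drop-out | completers = 24 × 0.80 | 19.2 per group, 38.4 in total |
| 24 recruits and 20 completers per group | drop-out = 1 − 20/24 | 16.7% |

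**Step 4: size of the consequence.** With equal groups and a given standard deviation, the standard error of the difference in means is proportional to √(2/n). Moving from 20 to 19.2 per group multiplies it by √(20/19.2) = 1.02, a loss of precision of about 2%. This ratio needs no assumed effect size. It applies to an analysis of patients with observed data.

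**The case against.** The strongest reply is that nothing turns on the difference between 19 and 20. The 20 has no power calculation behind it and section 2.6 says so, so no claimed power or decision threshold is lost. In addition, the intention-to-treat analysis with last observation carried forward is meant to include all 48, which is 24 per group. Both points stand. They make the error small and limit it to patients with observed data. They do not reconcile the three figures, and section 2.6 itself counts patients after drop-out.

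Four stronger readings are tempting, and the document does not support them.

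- *The design will probably miss its own target.* If each patient independently has an 80% chance of completing, the chance of at least 20 completers in both groups is about 21% with 24 recruited per group. With the correctly inflated 25 it is still only about 38%. Much of the low figure is therefore chance variation around a target set at the expected value, and it is a poor measure of this error.
- *The trial can detect only about 0.9 SD.* An unadjusted two-sided 5% t-test with 20 per group does need about 0.91 SD for 80% power. The plan names ANCOVA for the primary outcome and an intention-to-treat set of all 48, so that figure does not describe the planned test and should not be written into the protocol as its detectable difference.
- *A significant result would not count.* Small numbers do not raise the type I error of a two-sided 5% test on one named primary outcome. A significant difference would remain a valid rejection of the null hypothesis.
- *The Discussion claims that this sample size can confirm efficacy.* Section 3 says that "the efficacy of acupuncture could be confirmed if the results of the acupoint group prove superior to those of the NA control group". That sentence is conditional, closes a paragraph on the choice of sham control and on blinding, and says nothing about sample size. It sits a little awkwardly beside the preparatory role described in section 2.6, but this is a matter of tone and not an error.

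**Conclusion.** The arithmetic in section 2.6 is wrong as written. At the stated 20% drop-out, 24 recruits per group give an expected 19.2 completers (38.4 in total), not 20 (40). The cause is multiplying by 1.2 where dividing by 0.8 was needed.

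The size is about one patient per group, or two recruits in 48 if the target were corrected to 50. The conclusion assumes only that the drop-out rate is a share of those recruited and that the 20 means patients left after drop-out, as the order of the two sentences in section 2.6 implies. It does not touch any stated power, the validity of the primary test, or the intention-to-treat set of 48. It is a minor but definite correction.

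**What to change.** Correct the sentence in section 2.6 without enrolling more patients, in one of two ways:

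- keep 48 recruits and 20% drop-out, and state about 19 completers per group; or
- keep 48 recruits and 20 completers per group, and state the drop-out allowance as 16.7%.

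If both 20 completers and 20% drop-out are to be kept, the consistent target is 25 per group (50 in total), at the cost of two more recruits. The first two options cost one sentence. The first makes the stated completer number slightly less favourable; the second relies on a lower assumed drop-out.

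Optionally, reword the Discussion's remark on confirming efficacy so that it matches the statement in section 2.6 that the trial will inform a definitive one. This is an editorial alignment and changes nothing in the design or analysis.

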### 2.7. Multimodal Data Acquisition

#### 2.7.1. MRI Data Acquisition

Patients will undergo brain MRI at prerandomization (baseline) and 4 weeks, 12 weeks, and 24 weeks after randomization. MRI scans will be performed with a 3.0-T MR scanner (Siemens AG, Germany) in the Dongzhimen Hospital affiliated to BUCM. The parameters of the sequences to be employed in this study are provided by the China Association of Brain Imaging. Sagittal structural images will be acquired using a magnetization-prepared rapid gradient-echo three-dimensional (3D) T1-weighted sequence with the following parameters: repetition time (TR)/echo time (TE) = 1900/2.13 ms, flip angle = 9°, inversion time = 1100 ms, resolution = 256 × 256, voxel size: 1.0 × 1.0 × 1.0, 1-mm slice thickness without slice gap.

RS-fMRI and task-fMRI will be performed using an echo-planar imaging (EPI) sequence with the following parameters: TR/TE = 2000/30 ms, flip angle = 90°, resolution = 64 × 64, FOV = 225 × 225, bandwidth = 2520, slice thickness = 3.5 mm with 0.7 mm slice gap, 31 axial slices, and voxel size: 3.5 × 3.5 × 3.5.

Diffusion tensor imaging (DTI) will be acquired with a diffusion-weighted, single-shot, spin-echo, echo-planar imaging sequence that uses 30 directions with *b* = 0 s/mm^2^ and *b* = 1000 s/mm^2^, slice thickness: 2 mm, gap = 0 mm, slices = 65,TR: 11000 ms, TE: 94 ms, matrix: 128 × 128, FOV: 256 × 256, and phase encode direction: *A* >> P.

All scans will be qualitatively reviewed by two radiologists to screen for possible brain lesions or structural abnormalities. fMRI data will be collected during the word-picture judgement task and at rest. fMRI data will be performed with the SPM12 (https://www.fil.ion.ucl.ac.uk/spm/software/spm12/) for MATLAB. Brain activation and connectivity changes will be compared between the two groups.

#### 2.7.2. EEG Data Acquisition

The 64-channel EEG recording and analysis system produced by the Neuroscan of Australia, E-prime 2.0 stimulation display software, scan data analysis software, SYNAMPS EEG amplifier, Fastrak 3D imaging digital instrument, Quick-Cap electrode cap, recording electrode, electrode paste, and Curry multichannel neuroimaging software will be used to collect EEG signals. EEG data in the resting state will be collected for 8 minutes, and event-related potentials (ERPs) will be collected during language task assessment for 8 minutes. The same word-picture judgement task used for the MRI will be applied to ERP collection. Patients will undergo an EEG at a different time on the same day as the MRI scan.

#### 2.7.3. Word-Picture Judgement Task

The patients will be trained before entering the fMRI scanner. They will complete a practice version of the word-picture judgement task paradigm in the computer. They need to perform the task and reach an accuracy criterion of 90% to ensure that the patients understand how to do the task in the scanner. Patients will view black and white line pictures and Chinese high-frequency nouns. The patients are required to press a mouse button when the picture and the noun appear on a white background. The patients are asked to press the left button if the picture and the noun express the same meaning; otherwise, they should right-click. The stimuli are presented in 60 blocks on a computer using E-prime 2.0. In the ERP experiment, there will be 120 blocks. Trial types within blocks are presented in a pseudorandomized order. During the MRI scanning, all patients are asked to lie quietly in the scanner with their eyes open, trying to avoid systematic thinking, and moving as little as possible. In task-state fMRI scanning, the patients are instructed to maintain a central view and try to not think of other things. During ERP testing, patients are asked to sit in front of the computer, and the surroundings will be kept quiet (Figure 4).

### 2.8. Outcome Measures

#### 2.8.1. Clinical Outcome Assessments

The primary outcome will be the change in the AQ score during the 12th week after randomization. For the assessment of language functioning, the WAB with the subtests spontaneous speech, auditory comprehension, repetition, and naming is included in the test battery. The WAB test will be conducted based on a previous study [40]. Secondary outcomes include four items, the details of which are listed in Table 1.

#### 2.8.2. Neuroplasticity Assessments

In this study, neuroplasticity changes between the two groups will be measured by MRI. Before acupuncture treatment, patients will complete the fMRI scan within 3 days. They will also have a follow-up fMRI scan within 3 days after the completion of their intervention and at 8 weeks and 16 weeks after the intervention (Figure 1). Brain activity and functional connectivity will be assessed under a resting state and a word-picture judgement task. Group differences in white matter integrity will be assessed using DTI.

#### 2.8.3. Assessment of Acupuncture Safety

Acupuncture is considered to be a generally safe procedure [41–43]; however, all adverse events will be recorded in every detail. In this study, acupuncture-related adverse events would mainly refer to broken needles, fainting due to the needling procedure, local infection, hematoma, and other events that can be caused by acupuncture (such as headache, dizziness, and insomnia).

#### 2.8.4. Quality Control

All practitioners will conduct the study according to the standard operating procedure of the study. We will conduct several simulations for our volunteers before the start of the study. During the study, regular meetings will be held to discuss issues raised by researchers or participants, the need to improve protocols, the side effects, and participant recruitment.

### 2.9. Statistical Analysis

#### 2.9.1. Clinical Data Analysis

All statistical analyses will be performed by a statistician from the Clinical Evaluation and Analysis Centre of Dongzhimen Hospital affiliated to BUCM using Statistical Package for the Social Sciences (SPSS) V.22.0. The statistician will be blinded to the allocation of groups. The level of significance is established at *α* < 0.05 with a two-tailed test. The main objective is to compare the change in the AQ score at week 12 from baseline between the acupoint group and the NA control group. The null hypothesis is that the acupoint group will show the same change as the NA control group, while the alternative hypothesis is that the acupoint group shows a greater improvement. Categorical data will be represented by percentages, whereas continuous data will be represented by the average, standard deviation, median, minimum value, and maximum value. For comparison with the baseline, a *t*-test or nonparametric test will be used for continuous data and nonparametric tests for categorical data. For comparison of two independent samples, if the residuals are normally distributed, the analysis of covariance (ANCOVA) will be used for the primary outcome and subgroup analysis stratified by aphasia severity, *t*-tests for other continuous data, and chi-square tests for categorical data; if the residuals are non-normally distributed, a nonparametric test will be used for both the continuous and categorical data. The results of the intention-to-treat (ITT) analysis will be used to assess the validity of the study as a whole. The ITT analysis will collect data from all the participants in this trial, and for those lost to follow-up, the last observation carried forward method will be implemented.

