## Abstract

**Background:**

Poststroke aphasia (PSA) is a disabling condition that decreases the quality of life, and the duration of the disease harms the quality of life of PSA patients. Acupuncture has been widely employed for PSA. There is some evidence for the immediate treatment efficacy of acupuncture for PSA; however, long-term results after acupuncture may be poorer.

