Acupuncture is an easy-to-use, low-cost adjunct to traditional SLT to enhance language outcomes in individuals with PSA. It is one of the main treatments of traditional Chinese medicine (TCM) and has been used for thousands of years. During the past decade, the results of several meta-analyses have concluded that acupuncture after stroke seems to be effective in improving PSA functional communication and language function [17, 18]; however, most of the studies did not assess therapeutic effects over extended periods. For acupuncture treatment, long-term efficacy is considered one of the most important therapeutic effects, which has been suggested by numerous clinical studies [19–25]. It represents the cumulative effect of positive achievements [16]. Long-term efficacy will allow the patient's therapeutic effects to accumulate (“more is better”). Our previous studies on the effects of acupuncture on PSA have shown that participants in the acupuncture group had lower severity than the control group in week 4, but the difference was not significant; however, a significant reduction in PSA severity during weeks 5 to 12 was noted [26]. In addition, we explored the traditional Chinese medical theory and acupuncture technique of this acupuncture programme [27, 28]. Acupuncture has also been shown to have long-term efficacy in chronic pain and tinnitus, which has shown effective therapeutic results [29, 30]. Therefore, we speculate that the long-term therapeutic effect for PSA will also be well maintained; however, the long-term efficacy of acupuncture compared with the placebo effect in patients with PSA has not been investigated.

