In terms of the current state of evaluation of aphasia, the requirements for a comprehensive evaluation of PSA have not yet been fully implemented. One of the important means was to evaluate the language characteristics of PSA, which is the major part of the evaluation; however, to date, this single evaluation approach is often insufficient. As such, neuropsychological tests in conjunction with in vivo measures may be more sensitive than neuropsychological tests alone in the assessment of brain structure and electrophysiology [31–33]. We introduce MRI and EEG for evaluation of the objective characteristics of PSA because the multimodal assessment of brain structure and function allows for a more objective evaluation of the recovery characteristics of patients with aphasia. Based on the previous study [34], we conducted a TCM syndrome evaluation of PSA patients and confirmed the relationship between linguistic features and TCM syndrome. Therefore, in this study, we have also introduced the evaluation of TCM syndrome to provide more comprehensive evidence of efficacy based on the combined evaluation of Chinese and Western medicine. For the reasons above, we propose to investigate whether acupuncture treatment on PSA has the value of maintaining long-term efficacy through this randomized controlled trial (RCT) with multimodal evaluation.

We designed an assessor- and participant-blinded RCT with PSA patients. Using NA acupuncture as a control, the trial aims to identify the efficacy of acupuncture by answering two questions: (1) what is the long-term efficacy and reliability of acupuncture as an intervention for PSA compared with the placebo effect? and (2) what interactions will be observed through an integrated evaluation of linguistic features, brain function, and TCM syndrome?

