It is worth mentioning that functional and structural brain alterations will be used as outcome measures. MRI allows for noninvasive evaluations of neural functional changes [48]. fMRI studies use two modalities, task-related and resting-state methods [49]. Task-related fMRI has revealed functional disturbances in individuals with aphasia. MRI may be more sensitive to smaller treatment effects. It can be used as a tool to assess the efficacy of acupuncture in treating aphasia. These analyses may identify whether neural efficiency is improved or the brain connectome is reorganized to achieve language enhancement. Electrophysiological methods, such as intracranially recorded EEG or ERP, are particularly promising to offer a mechanistic understanding of language formation processes. Compared with the language scales alone, the combination of in vivo measures of brain alterations in this study will be more sensitive in detecting acupuncture efficacy [50].

Therefore, this study can provide clinical evidence on the long-term efficacy of our acupuncture programme in patients with PSA and explore biomarkers for the recovery of function and the efficacy of acupuncture in patients with PSA through a multidimensional evaluation. This trial will fill the gaps in the evidence on the long-term efficacy of acupuncture for aphasia and provide a model for the multimodal evaluation of PSA.

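### The protocol asks about maintained long-term efficacy, but its one formal hypothesis stops at week 12, and the week-24 AQ has no stated inferential role and a weaker analysis

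*Protocol article*

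**What the plan says.** **The question.** The Introduction closes its rationale with "we propose to investigate whether acupuncture treatment on PSA has the value of maintaining long-term efficacy", and the first of its two numbered questions is "what is the long-term efficacy and reliability of acupuncture as an intervention for PSA compared with the placebo effect". The Discussion again describes the aim as long-term efficacy in maintaining speech. The Abstract gives the worry behind it, that "long-term results after acupuncture may be poorer", and the Discussion promises that "This trial will fill the gaps in the evidence on the long-term efficacy of acupuncture for aphasia".

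**The test.** Section 2.8.1 states: "The primary outcome will be the change in the AQ score during the 12th week after randomization". Section 2.9.1 puts the aim this way: "The main objective is to compare the change in the AQ score at week 12 from baseline between the acupoint group and the NA control". It gives one null and one alternative hypothesis, both for the AQ change from baseline to week 12.

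**The visits.** Acupuncture and speech therapy run for 4 weeks (sections 2.5 and 2.5.3). Table 1 schedules the Western Aphasia Battery, which yields the AQ, at baseline and weeks 4, 12 and 24.

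**The methods.** Section 2.9.1 lists comparisons with baseline and comparisons of two independent samples. If residuals are normal, ANCOVA is for the primary outcome and the severity subgroups, and t-tests are for other continuous data. Participants lost to follow-up have their last observation carried forward.

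**The background.** The Introduction reports that the group's earlier study found no significant difference at week 4, but that "a significant reduction in PSA severity during weeks 5 to 12 was noted". It adds that long-term efficacy against placebo has not been investigated.

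**The concern.** Maintenance is a statement about what happens to an effect after treatment stops. A single contrast from baseline to week 12 shows whether the arms differ 8 weeks after the last session. It does not show whether that difference is growing, stable or shrinking, or whether anything remains at week 24.

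Week 24 is the visit that reaches furthest, and the protocol gives it no place in the hypothesis and no rank among the secondary results. On the stated methods it also gets a less efficient analysis than week 12. A positive week-12 result could then be described as long-term or maintained efficacy without the later data having been given a say. The Discussion itself notes some spontaneous recovery in the subacute phase, so a gap that narrows as controls improve is possible. That last step is an inference, not something the protocol states.

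**Working it through.** **1. Time covered.** Week 12 − week 4 = 8 weeks after treatment. Week 24 − week 4 = 20 weeks. 8/20 = 40% of the observed post-treatment period.

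**2. What week 12 can distinguish.** Assume three sets of between-arm AQ differences, for illustration only:

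| Pattern | Week 4 | Week 12 | Week 24 |
|---|---|---|---|
| Fading | 8 | 5 | 0 |
| Maintained | 5 | 5 | 5 |
| Emerging | 1 | 5 | 8 |

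All three give the same primary result, 5 points. The change in the difference from week 4 to week 24 is 0 − 8 = −8, 5 − 5 = 0 and 8 − 1 = +7. Only the other visits separate them.

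**3. What carrying forward does.** Section 2.6 allows for 20% drop-out. Its own figures reproduce as 20 × 1.2 = 24 per group, 48 in all. Suppose, as an extreme, that all of the 20% leave just after week 4 in both arms and would otherwise have followed the arm average. Under the fading pattern the carried-forward difference at week 24 is 0.8 × 0 + 0.2 × 8 = 1.6 points, where the true value is 0. A carried week-4 score has zero change from week 4 by construction, so it looks like maintenance whatever happened to the patient.

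**4. Precision at week 24 and for change from week 4.** Inputs: 20 per arm (section 2.6) and two-sided 0.05 (section 2.9.1). Assumptions: equal AQ standard deviation (SD) at each visit, correlation ρ between visits, normal approximation. The protocol gives neither an SD nor ρ, so results are in SD units over a range of ρ.

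- Difference in change between two visits: half-width = 1.96 × √(2(1 − ρ)) × √(2/20).
- ANCOVA adjusting for baseline AQ: half-width = 1.96 × √(1 − ρ²) × √(2/20).
- 1.96 × √(2/20) = 1.96 × 0.316 = 0.62.

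| ρ | Change score, unadjusted | Baseline-adjusted ANCOVA |
|---|---|---|
| 0.5 | 0.62 | 0.54 |
| 0.7 | 0.48 | 0.44 |
| 0.8 | 0.39 | 0.37 |
| 0.9 | 0.28 | 0.27 |

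The protocol does not say whether the t-test would take the change or the week-24 score itself. On the score itself the half-width is 0.62 at every ρ. ANCOVA is therefore never worse here. Its gain is modest against a change score and large against the raw score when ρ is high. The first column also applies to the change from week 4 to week 12 or 24.

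**5. Stated contrasts set against the question.** Comparisons with baseline describe change within an arm. Two-sample comparisons describe the gap at a visit. None of the stated comparisons takes week 4 as its reference, and none is named for week 24.

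**The case against.** Several stronger readings are tempting, and the documents do not support them.

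- **That week 12 is the only objective.** Section 2.9.1 calls it the main objective, the Introduction poses two questions, and the AQ at week 24 is collected and could fall under the generic two-sample test.
- **That persistence goes untested.** A difference from sham 8 weeks after the last session is an off-treatment effect. Table 1 labels weeks 5 to 12 as follow-up, and the protocol sets no threshold that excludes week 12 from being long-term.
- **That week 12 merely repeats the earlier study.** The Introduction says the comparison with placebo is still open, and the earlier pattern is a sensible reason for choosing week 12.
- **That the Discussion contains a rule licensing a long-term claim from week 12 alone.** The sentence about confirming efficacy if the acupoint group proves superior justifies the sham design. It names no visit and is not a decision rule.

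It is also fair to say that an article condenses the protocol and that the analysis plan is not shown. The bare absence of a contrast from week 4 therefore carries little weight. Nor could a significance test on that contrast establish maintenance: under the maintained pattern its expected value is zero, and no margin is set.

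All of this stands. What it leaves untouched is the mismatch between things the article does state: the maintenance question, the single week-12 hypothesis, and a methods paragraph that reserves ANCOVA for the primary outcome and severity subgroups.

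**Conclusion.** The point holds in limited form. The week-12 primary contrast is a valid test of an off-treatment effect against sham and answers part of the stated question. It covers 8 of 20 observed post-treatment weeks and cannot separate a lasting effect from a fading one. The week-24 AQ could help to do so, but it has no stated inferential role and, as written, a less efficient analysis whose missing values are carried forward.

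This rests on reading the primary outcome as week 12 only, so that the week-24 AQ counts among the other continuous data, and on taking baseline AQ as the ANCOVA covariate, which section 2.9.1 does not name. The AQ patterns, the drop-out timing and the correlations are illustrations. They show what the design can and cannot distinguish, not what will happen. The primary test does not need to change. What is affected is how far the conclusion may go.

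**What to change.** 1. Keep the AQ change from baseline to week 12 as primary.
2. Name the AQ change from baseline to week 24 as the key secondary outcome. Test it only if week 12 is significant, at the same two-sided 0.05 and with the same ANCOVA adjusted for baseline AQ. The fixed order keeps the error rate for the pair at 0.05.
3. Report the between-arm difference in AQ change from week 4 to week 12 and from week 4 to week 24 as estimates with 95% intervals. Do not present them as significance tests of maintenance, and do not read carried-forward week-4 scores as evidence of no loss.
4. State that conclusions worded as long-term or maintained follow the week-24 estimate and its interval. If these do not support the claim, limit the conclusion to 8 weeks after treatment.

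The cost is analysis and wording only, because every assessment is already scheduled. The downsides are a stricter condition for the long-term claim and imprecise estimates with about 20 per arm, which may not separate fading from maintained.
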